# Treatment of haemorrhoids: rubber band ligation or sclerotherapy (THROS)? Study protocol for a multicentre, non-inferiority, randomised controlled trial

**DOI:** 10.1186/s13063-023-07400-2

**Published:** 2023-06-03

**Keywords:** Haemorrhoidal disease, Grade 1–2 haemorrhoids, Rubber band ligation, Sclerotherapy, Patient-related outcome measures, PROMs

## Abstract

**Introduction:**

Haemorrhoidal disease (HD) is a common condition with significant epidemiologic and economic implications. While it is possible to treat symptomatic grade 1–2 haemorrhoids with rubber band ligation (RBL) or sclerotherapy (SCL), the effectiveness of these treatments compatible with current standards has not yet been investigated with a randomised controlled trial. The hypothesis is that SCL is not inferior to RBL in terms of symptom reduction (patient-related outcome measures (PROMs)), patient experience, complications or recurrence rate.

**Methods and analysis:**

This protocol describes the methodology of a non-inferiority, multicentre, randomised controlled trial comparing rubber band ligation and sclerotherapy for symptomatic grade 1–2 haemorrhoids in adults (> 18 years). Patients are preferably randomised between the two treatment arms. However, patients with a strong preference for one of the treatments and refuse randomisation are eligible for the registration arm. Patients either receive 4 cc Aethoxysklerol 3% SCL or 3 × RBL. The primary outcome measures are symptom reduction by means of PROMs, recurrence and complication rates. Secondary outcome measures are patient experience, number of treatments and days of sick leave from work. Data are collected at 4 different time points.

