### Outcomes

#### Primary outcomes

The primary outcome measures are treatment efficacy measured through PROMs according to the ESCP core outcome set of symptom reduction, subjective recurrences and complications (Table 1). The follow-up period for this outcome set is 6 months, and data will be collected at 4 different time points during this period (baseline, 1 week, 6 weeks and 6 months after the first procedure).

**Table 1 Tab1:** Primary and secondary outcome measures

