	**Tools of measurement**
**Primary outcomes**	
*Patient-related outcomes*	PROM (minimal score 5, maximum score 25): The lower the score the better the result
- Blood loss	Likert scale – 1 (not at all) to 5 (very much)
- Pain	Likert scale – 1 (not at all) to 5 (very much)
- Prolapse	Likert scale – 1 (not at all) to 5 (very much)
- Itching	Likert scale – 1 (not at all) to 5 (very much)
- Soiling	Likert scale – 1 (not at all) to 5 (very much)
	HISS (minimal score 0, maximum score 20)
- Impact on daily activities	Scale – 0 (no impact at all) to 10 (highly impacted on daily activities)
- Satisfaction with treatment	Scale – 0 (not at all satisfied) to 10 (very satisfied)
*Complications*	
Incontinence	Wexner Fecal Incontinence Score
Abscess	Physical examination^a^
Fistulation	Physical examination^a^
Urine retention	Bladder scan
Anal stenosis	Physical examination^a^
Anal fissure	Physical examination
Arterial bleeding	Physical examination
Thrombosed haemorrhoid	Physical examination
*Recurrence*	Subjective return of initial symptoms

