### Sample size calculation

The sample size is based on a success percentage of 70% in both treatment arms, in terms of symptom reduction. Based on the available literature from Cocorullo et al. [6], we will perform a non-inferiority analysis with a two-sided significance (alpha 2.5%), 80% power and a 10% non-inferiority limit. Consequently, a total of 330 randomised patients are required per arm, so 660 randomised patients in total.Significance level (a) = 2.5%Power (1-beta) = 80%Non-inferiority limit = 10%Proportionality group A = 70%Proportionality group B = 70%Sample size required per group = 330Total sample size required = 660

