## Statistical analysis

Both intention-to-treat and per-protocol analyses shall be carried out. Crossover is not desirable, but possible if deemed necessary by the treating physician. Crossover will be considered as a secondary outcome measure. Analyses will be carried out using SPSS version 26.0. A *p*-value of 0.05 or less is considered as statistically significant.

For the primary outcome, any reduction in a PROM/PREM score per symptom is scored as ‘improvement’ when considering the results as binary success or not. Analysis of primary outcomes will be tested with chi-square test or Fisher’s exact test. Considering there are four time points for the outcomes, these time points will be taken into account during the analysis. Descriptive methods will be used to check the quality of the data, homogeneity of the two treatment groups and primary and secondary endpoints. Significant confounders will be identified using multivariate analysis. Categorical variables will be presented as percentages and continuous variables will be presented as means with their confidence intervals. To examine gender differences, an additional analysis will be carried out. An interim analysis will take place after the first 300 patients have been randomised and 6-month follow-up is completed. Both the number of patients who experienced complications and the number of patients with recurrent symptoms after 6 months will be evaluated between the two groups. If there are significant differences, then the entire study group will discuss these findings and discuss whether the study can be continued.

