## Discussion

The THROS study is the first large multicentre randomised trial to study the difference in effectivity between RBL and SCL for the treatment of grade 1–2 HD. Primary and secondary outcomes consist of both objective and subjective patient-reported outcomes. In this non-inferiority trial, we hypothesize that SCL is non-inferior to RBL with regard to effectiveness, patient experience, complications and recurrences.

As HD is one of the most common conditions in the general population, with an annual incidence of 5%, it represents a significant epidemiologic and economic burden. Most patients experience blood loss and for some patients, this blood loss can cause symptomatic anaemia. Patients with grade 1–2 haemorrhoids may also experience other symptoms like itchiness, pain or soiling and, because of additional stigma and shame, it represents a high burden that affects the quality of life.

However, patients’ experience of HD symptoms and its burden on everyday life is in contrast with the surgeon’s experience in which it is perceived as a ‘simple’ diagnosis with a relatively ‘simple’ solution/treatment. Therefore, surgeons and proctologists are driven to treat their patients with less invasive, but most effective method, in which the patients’ experience of the treatment also plays an important role. This is especially so considering that for the majority of cases, a singular treatment is insufficient to fully treat the HD.

In case of more severe (grade 3–4) or recurrent HD, there are several multicentre randomised controlled trials studying the effect of different treatment options. Both the HollAND and Napoleon trial, which were forced to stop prematurely due to inclusion difficulties, are currently in the follow-up phase. Both studies compare more invasive techniques (haemorrhoidectomy or sutured mucopexy) with RBL [14, 15]. However, symptomatic grade 1–2 HD are far more common in the general population and so an answer as to what the best and most appropriate minimal invasive treatment option is, is needed.

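### Three unranked primary outcomes carry the non-inferiority hypothesis, but margin and power are set for symptom reduction alone, at an unnamed visit

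*Protocol article*

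**What the plan says.** All references are to the protocol article.

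- **Primary outcomes.** The abstract lists three without ranking: "The primary outcome measures are symptom reduction by means of PROMs, recurrence and complication rates". The Primary outcomes section repeats them as the "ESCP core outcome set of symptom reduction, subjective recurrences and complications". Table 1 expands the list to five symptoms, two HISS items, eight complications and recurrence, the last defined as "Subjective return of initial symptoms".
- **Hypothesis.** The abstract begins "The hypothesis is that SCL is not inferior to RBL in terms of symptom reduction" and continues with patient experience, complications and recurrence, joined by 'or'. The Discussion uses 'and': "we hypothesize that SCL is non-inferior to RBL with regard to effectiveness, patient experience, complications and recurrences".
- **Sample size.** "The sample size is based on a success percentage of 70% in both treatment arms, in terms of symptom reduction". The calculation is described as a "non-inferiority analysis with a two-sided significance (alpha 2.5%), 80% power and a 10% non-inferiority limit" and gives 330 per arm. No visit is attached to the 70%.
- **Visits.** Table 2 schedules the PROM at baseline and at 1 week, 6 weeks and 6 months, recurrence at 6 weeks and 6 months, and complications at 6 weeks. The Statistical analysis section says only: "Considering there are four time points for the outcomes, these time points will be taken into account during the analysis". It plans chi-square or Fisher tests of the primary outcomes, with a significance threshold of 0.05.

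**The concern.** A non-inferiority claim needs an outcome, a time, a margin and a decision rule. Here the claim spans three primary outcomes, two of which have no margin, and nothing says whether one success is enough or all are needed. Non-inferiority on recurrence or complications cannot be tested as written. For symptom reduction, three post-baseline visits are available and none is designated.

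The visits are not interchangeable. The 1-week questionnaire recalls the week that contains the procedure. The 6-week assessment is made by an unblinded physician. The 6-month interview is by telephone, with a researcher who is meant to be blinded. Results could differ between visits, and the plan leaves open which of them decides the trial.

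Recurrence adds a problem of interpretation. A return of symptoms presupposes that they went away. If patients who never improved are not counted as recurrences but stay in the denominator, a less effective treatment can show less recurrence.

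**Working it through.** **1. Reproduce the stated sample size.** Inputs from Sample size calculation: 70% in both arms, margin 0.10, alpha 0.025 taken one-sided, power 0.80.

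n per arm = 2p(1−p)(z₀.₉₇₅ + z₀.₈₀)² / margin² = 2 × 0.70 × 0.30 × (1.960 + 0.842)² / 0.10² = 329.7, so 330. This matches. Power at 330 is 80.0%. A literal two-sided 2.5% would need 400, so the figure rests on one-sided 2.5%.

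**2. If all three must succeed.** Each test at one-sided 2.5% keeps the error of the joint claim controlled; power is what changes. The protocol gives no margin for recurrence or complications, so the 10-point margin is borrowed for both (assumption), with equal true rates in the arms. Rates come from the Introduction's literature ranges: recurrence 10–18% (ligation) and complications 34–49% (sclerotherapy).

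Power = Φ(0.10/SE − 1.960), with SE = √(2p(1−p)/330).

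| Outcome | Rate | SE | Power |
|---|---|---|---|
| Symptom reduction | 70% | 0.0357 | 0.800 |
| Recurrence | 10% | 0.0234 | 0.990 |
| Recurrence | 18% | 0.0299 | 0.917 |
| Complications | 8% | 0.0211 | 0.997 |
| Complications | 34% | 0.0369 | 0.774 |
| Complications | 49% | 0.0389 | 0.729 |

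Joint power under independence:
- Recurrence 10%, complications 34%: 0.800 × 0.990 × 0.774 = 0.613 (61%).
- Recurrence 18%, complications 49%: 0.800 × 0.917 × 0.729 = 0.535 (53% from unrounded components).
- Most favourable case examined, 10% and 8% (the low end of the ligation complication range): 0.800 × 0.990 × 0.997 = 0.790 (79%).

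Whatever the correlation, joint power cannot exceed the weakest component. That caps it at 77% and 73% in the first two cases.

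**3. If any one suffices.** The ceiling on one-sided error, with independent comparisons each at its margin, is 1 − 0.975^k.
- Three outcomes: 1 − 0.975³ = 7.3%.
- Scheduled outcome-visit combinations, PROM 3 + recurrence 2 + complications 1 = 6: 1 − 0.975⁶ = 14.1%.

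**4. Recurrence, as an illustration.** Suppose 80% improve in one arm and 60% in the other, and 20% of improvers relapse in each (all assumed). With all randomised patients as denominator, recurrence is 0.80 × 0.20 = 16% against 0.60 × 0.20 = 12%, so the less effective arm looks better. Among improvers only, it is 20% in both.

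**The case against.** **What stands.** The sample size section ties its figures expressly to symptom reduction, its arithmetic is right, and the document never claims 80% power for a joint result. The abstract's 'or' follows a negative and may simply mean all four. A statistical analysis plan may settle the decision rule and the handling of visits. The joint-power range depends on a borrowed margin, literature rates and independence. The error ceilings are high because repeated assessments of the same patients are correlated.

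**What does not answer the point.** The set of primary outcomes, the breadth of the hypothesis and the basis of the sample size are fixed in this document. Choosing among those outcomes later is exactly the freedom at issue. The core outcome set calls for all three to be reported, which secondary status still allows.

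**Stronger readings that a reader might infer, but the documents do not support:**
- That the 2.5% and the 80% fail together. They fail under different rules: power if all must succeed, error if any suffices.
- That error reaches 20% (three outcomes at three visits, 1 − 0.975⁹). Table 2 does not schedule recurrence at 1 week and schedules complications only at 6 weeks.
- That it reaches 32% (five symptoms at three visits, 1 − 0.975¹⁵). This treats each symptom as a separate test, whereas Treatment efficacy defines improvement on the domain score, and it assumes independence among symptoms of the same patient.
- That joint power is 51% (0.8³). The three outcomes do not each have 80% power at 330 per arm.
- That recurrence necessarily favours the worse arm. Neither Table 1 nor Treatment efficacy states a denominator. In the illustration that arm is also 20 points worse on symptom reduction, well outside the 10-point margin.

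**Conclusion.** The point holds in a limited form and should be acted on. The stated operating characteristics cover symptom reduction at an unspecified visit; they do not cover the hypothesis as the abstract and Discussion word it. Two of the three primary outcomes have no margin, so no exact power or error exists for the overall claim, only ranges under stated assumptions.

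An all-must-succeed rule costs power. The loss is large at complication rates of 34–49% and about one percentage point in the most favourable case. An any-success rule costs error control, up to the ceilings shown. The recurrence problem is conditional on the denominator and on how never-improvers are counted. The 330 per arm itself is not in question.

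**What to change.** Name one primary endpoint that matches the existing sample size: PROM symptom success at 6 months, as the difference in proportions, sclerotherapy minus rubber band ligation. Use the 10-point margin and one-sided 2.5%, so that non-inferiority is concluded when the lower limit of the 95% confidence interval lies above −10 points. Make the other PROM visits, the HISS items, complications and recurrence secondary, reported as differences with 95% confidence intervals and without a non-inferiority claim. Replace stand-alone recurrence with persistent or recurrent symptoms among all randomised patients. If the investigators prefer to keep three primary outcomes, each needs its own margin and power, with an explicit all-or-any rule.

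Costs and limits to state:
- No extra patients or data collection are needed, but this is a substantive amendment to a trial registered and approved in 2020, and complications and recurrence lose primary status.
- Patients know their treatment at every visit, and Recruitment and blinding concedes that full blinding of the interviewer is not guaranteed. The 6-month visit is better protected than the 6-week visit but is not blinded.
- Trial design and Interventions permit crossover after at least two treatments, so 6-month results can follow crossover. Under intention to treat this may pull the arms together and favour non-inferiority. The per-protocol analysis, already planned, must therefore also support the conclusion.

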**Discussion:**

The THROS trial is the first large multicentre randomised trial to study the difference in effectivity between RBL and SCL for the treatment of grade 1–2 HD. It will provide information as to which treatment method (RBL or SCL) is the most effective, gives fewer complications and is experienced by the patient as the best option.

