## Methods and analysis

### Trial design

The THROS trial is a non-inferiority, multicentre, randomised controlled trial with two parallel groups: RBL vs. SCL. The allocation ratio is 1:1. Crossover is possible for patients who experience no improvement of symptoms after at least two treatments within one treatment arm. It is expected that when two treatments have not reduced symptoms and a third treatment is necessary, both patients and surgeons are inclined to try a new treatment option. So crossover rate is also indicative for treatment success. Also, when patients have a strong preference for one of the two treatment arms and refuse randomisation, then registration in the preference arm is allowed. All patients’ symptoms could not be effectively managed by conservative treatment, which included dietary changes, laxatives, and lifestyle improvements. Conservative management was the first step of therapy in all cases. After eligibility has been established and patients have given their written informed consent, allocation or registration to one of the two treatment arms is possible. Data will be analysed on both ‘intention to treat’ and ‘per protocol’ basis.

The trial was registered at the Dutch Trial Register (NL8377). The protocol was drafted in accordance with the Standard Protocol Items: Recommendations for Interventional Trials statements (SPIRIT) [12].

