For the treatment of grade 1–2 HD, there are several options described in the literature and some of them are relatively new [16–19]. The THROS trial focuses on two less invasive treatment methods and it will provide us with information as to which commonly used treatment method (RBL or SCL) of grade 1–2 HD is the most effective, gives fewer complications and is experienced by the patient as the best option. Considering the available literature on SCL and RBL, we expect the efficacy and complication rates to be equal. However, in most cases of SCL or RBL therapy, repeated procedures are necessary to achieve acceptable symptom reduction, and it is for that reason that it is very important to investigate the patients’ experience of treatment. In current literature, there is limited available evidence regarding patient experience, except for pain scores [6]. Therefore, it is of even greater importance to compare both treatments in other domains, with the use of the recently developed PROM-HISS questionnaire [11, 13].

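### The article says the trial will inform which treatment is most effective, but it is designed and sized for non-inferiority, and its analysis section names only tests of difference that never use the 10-point limit

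*Protocol article*

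**What the plan says.** **What the trial is said to deliver.** Abstract, Discussion: "It will provide information as to which treatment method (RBL or SCL) is the most effective, gives fewer complications". The main Discussion says the same in nearly the same words.

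**What is hypothesised.** Abstract, Introduction: "The hypothesis is that SCL is not inferior to RBL in terms of symptom reduction", with patient experience, complications and recurrence also listed. The main Discussion: "we hypothesize that SCL is non-inferior to RBL with regard to effectiveness, patient experience, complications and recurrences". These two places give the direction of the question. Trial design names the non-inferiority type and the two groups without a direction: "The THROS trial is a non-inferiority, multicentre, randomised controlled trial with two parallel groups: RBL vs. SCL".

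**What it is sized for.** Sample size calculation: "The sample size is based on a success percentage of 70% in both treatment arms, in terms of symptom reduction". The same section promises "a non-inferiority analysis with a two-sided significance (alpha 2.5%), 80% power and a 10% non-inferiority limit" and arrives at 330 per arm, 660 in total. No other outcome is sized.

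**What is expected.** Discussion: "we expect the efficacy and complication rates to be equal".

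**How it will be analysed.** The Statistical analysis section compares the primary outcomes with a chi-square or Fisher's exact test and takes p of 0.05 or less as significant. It does not mention the 10-point limit or the confidence interval of a difference between arms.

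**The concern.** Three parts of the article answer three different questions. The closing statements speak of ranking the two treatments. The hypothesis and sample size ask whether SCL is not worse than RBL by 10 points. The analysis section tests whether the arms differ at all.

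If the authors' expectation of equal rates is right, the trial's positive result is that SCL is non-inferior, which names no most effective treatment. A chi-square test followed as written does not deliver that result either: a non-significant p-value does not establish non-inferiority, and a significant one does not say on which side of the limit the difference lies. Results are meant to reach coloproctological associations and guidelines, so the type of conclusion the trial can support should be clear.

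**Working it through.** **1. Inputs.** Success 70% in both arms, limit 10 points, alpha 2.5%, power 80%, 330 per arm (Sample size calculation); 1:1 allocation (Trial design); p of 0.05 or less (Statistical analysis); cited complication rates of 8–80% for RBL and 34–49% for SCL (Background and rationale). No dropout is assumed.

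**2. The plan's own figure.** n per arm = (1.960 + 0.8416)² × (0.7×0.3 + 0.7×0.3) / 0.10² = 7.849 × 0.42 / 0.01 = 329.65, so 330. It reproduces with a one-sided alpha of 2.5%, which matches a two-sided 95% confidence interval. A literal two-sided 2.5% (one-sided 1.25%) would give 400.

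**3. What a test of difference does with the same data.** With both rates near 70%, the half-width of the 95% interval is 1.96 × √(0.42/330) = 0.070, or 7.0 points. Non-inferiority then needs an observed SCL minus RBL above about −10 + 7 = −3 points. A significant difference needs an observed gap beyond about ±7 points.

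| Observed SCL − RBL | Approximate 95% interval | Difference test | Against the 10-point limit |
|---|---|---|---|
| 0 | −7 to +7 | not significant | non-inferior |
| −5 | −12 to +2 | not significant | non-inferiority not shown |

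The test of difference gives the same answer in both rows. The non-inferiority question has opposite answers.

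**4. Power to show a difference in success.** Power = Φ((|d| − 1.96 × SE0) / SE1), with SE0 from the pooled rate and SE1 from the two separate rates, n = 330 per arm. For 70% against 75%: SE0 = √(2 × 0.725 × 0.275 / 330) = 0.03476, SE1 = √((0.21 + 0.1875) / 330) = 0.03471, so Φ((0.05 − 0.0681) / 0.0347) = Φ(−0.522) = 30%.

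| True gap from 70% | Other arm higher | Other arm lower |
|---|---|---|
| 3 points | 13% | 13% |
| 5 points | 30% | 28% |
| 7 points | 53% | 48% |
| 9 points | 76% | 68% |
| 10 points | 84% | 77% |

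Solving for 80% power gives 9.5 points upward (70% against 79.5%) and 10.4 points downward (70% against 59.6%). If the true rates are equal, a significant difference arises only as the 5% type I error.

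**5. Complications.** The same formula, solved for 80% power from several base rates:

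| Base rate | Detectable decrease | Detectable increase |
|---|---|---|
| 8% | 5.0 points | 6.9 points |
| 20% | 8.0 points | 9.4 points |
| 34% | 9.9 points | 10.6 points |
| 49% | 10.8 points | 10.8 points |

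The 8%, 34% and 49% are ends of the cited ranges; 20% is an illustrative value inside the RBL range.

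**The case against.** The quoted sentences are closing prose. They say the trial will provide information, which is softer than a promise to show which treatment is best, and the Objectives section is neutral. Equal rates are a normal planning assumption for a non-inferiority trial and do not bar a later superiority reading. The analysis section does give a rule for claiming a difference, p of 0.05 or less, and the order of testing is often left to an analysis plan. All of this is fair, and it lowers the weight of the point.

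It does not remove the conflict inside the document. The sample size section commits to a non-inferiority analysis against a 10-point limit, while the analysis section names a different method for the primary outcomes. That is a conflict between two stated methods, more than a detail deferred to an analysis plan.

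Several stronger readings are tempting and are not supported:

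- That the trial cannot rank the arms unless they differ by about 9 points. The 9.5 to 10.4 points are true differences detectable with 80% power. An observed gap of about 7 points would be significant, and smaller true gaps keep some power.
- That power on complications is necessarily low. That follows only from base rates of a few per cent, below the cited ranges. At 20% against 34%, for example, power is 98%.
- That any ranking would be wrong by construction. That holds only if the true rates are exactly equal.
- That a small observed lead would be published as most effective. Nothing in the document says so.

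**Conclusion.** The point holds as a mismatch between the advertised conclusion, the design and the named analysis. The sample size is arithmetically right for its non-inferiority purpose. It gives limited power to show a modest difference in success: 28–30% at 5 points, and 80% only at a true gap of about 9.5 points upward or 10.4 downward. Complications are not sized at all, and what could be detected there runs from about 5 to 11 points over base rates of 8–49%.

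The more consequential half is the analysis section: followed as written, it yields a test of difference that cannot deliver the stated non-inferiority conclusion. The ranking language taken alone is a matter of wording.

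The figures assume 70% as the reference success rate, two-sided 5% for a superiority statement (from the analysis section), 330 analysed per arm and normal approximations. Any dropout would widen the detectable differences.

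**What to change.** In the Statistical analysis section, state that the primary symptom-reduction comparison is the difference in success proportions, SCL minus RBL, with a two-sided 95% confidence interval. Judge it first for non-inferiority: the lower bound must lie above −10 points. Only if that is met, read the same interval for superiority, which is shown if it excludes zero. This fixed order costs no alpha and no patients, and it agrees with the one-sided 2.5% that reproduces the 330 per arm.

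Report complications as a difference between arms with a 95% confidence interval.

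Reword the closing statements in the abstract and the Discussion to say that the trial assesses whether SCL is non-inferior to RBL. Keep the outcomes named in the hypothesis (symptom reduction, patient experience, complications, recurrence), and note that the trial is not sized to rank the arms. Do not write in a number of points below which ranking is said to be impossible.

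The cost is text only. The downside is a less ambitious advertised conclusion.
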